### **6.3 Multiplicity**

The primary endpoint is the maximum post-dose MCA mean flow velocity.

Whilst no formal multiplicity adjustments will be made amongst the secondary endpoints, the two key secondary endpoints are:

- 1) Modified Rankin Score at 90 days
- 2) GOSE score at 90 days

Individual BICRO subscales will not be considered statistically significant unless the overall BICRO score is also statistically significant at the same timepoint.

The TCD data will be analysed in advance of the other secondary endpoints. However, given that each endpoint will be analysed only once no adjustments will be made to the significance levels for each endpoint.

### **6.4 Analysis of the Primary Endpoint**

All TCD endpoints will be  $\log_e$ -transformed prior to analysis including baseline values. The primary endpoint of maximum post-dose MCA mean flow velocity will be analysed using an Analysis of Variance (ANOVA) model with terms for treatment, baseline (as defined in Section 5.1), WFNS grade (1-3 v 4-5), hypertension (yes vs no), surgical procedure (clipping vs coiling vs none), log-CRP and age fitted as a continuous covariate. The statistical significance of treatment will be based on type III sums of squares. The supplementary analyses of the mean of the 3 largest post-dose MCA mean flow velocities and the maximum post-dose Lindergaard ratio will use the same methods.

The maximum MCA mean flow velocity per timepoint will be analysed using a mixed model repeated measures (MMRM) approach with visits grouped, relative to date of Ictus, as Days 3-4, 5-6, 7-9, 10-14, 15-21, 22-28 and baseline covariates as defined for the primary analysis. Treatment effects for each visit will be obtained from the same model using the corresponding treatment-by-visit estimate. The MMRM will include terms for treatment, visit, treatment-by-visit, baseline-by-visit, covariates and observations blocked by subject. An unstructured covariance matrix will be used to model the within-subject error, along with restricted maximum likelihood and the Kenward-Roger approximation to estimate the degrees of freedom. If the model will not converge with an unstructured covariance matrix, heterogeneous Toeplitz and Toeplitz patterns will be tried in that order until the model will converge.

An example of the corresponding SAS code is given below

```
PROC MIXED data=data1 method=reml;
  CLASS trt vis pat wfns htn surg;
  MODEL lnTCD=base trt vis trt*vis base*vis age wfns htn surg lcrp / ddfm= KR;
```

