### 3 Study Design

The study is a randomised, double-blind, parallel-group design comparing SFX-01 (300 mg bd) administered for up to 28 days versus Placebo control in 90 patients who meet the per-protocol criteria for efficacy analyses, who have had a SAH and are referred to neurosurgical units for tertiary care.

Treatment is taken twice-daily either orally or via nasogastric tube (NG). For the first 20 patients, treatment duration is determined by the length of time spent in tertiary care (up to Day 28 post ictus). Following a DSMB review (as per protocol) for all subsequent patients the intended treatment duration is 28 days regardless of whether they remain in tertiary care for the full 28-day period. After treatment all patients are then followed up at discharge from the neurosurgical unit and then subsequently on Day 28, Day 90 and Day 180 post ictus.

A separate and more detailed investigation (sub-study) of the pharmacokinetic properties of SFN parent drug, and the primary metabolite, both in CSF and blood is also undertaken. This will involve up to 12 patients who have an External Ventricular Drain (EVD) fitted as part of their normal standard of care and is undertaken on two separate occasions within the first 7 days post ictus.

The protocol was amended part way through recruitment to stratify the randomisation by WFNS score (1-3 v 4-5) and centre.

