#### 3.1 Sample Size

Following protocol amendment 5, the sample size was increased from 90 to up to 120 patients in order to provide 90 who would meet the per protocol criteria and be evaluable for the primary efficacy analysis. Furthermore, this protocol amendment also specified that patients who had potentially received insufficient or incorrect study medication may be replaced.

If the standard deviation is approximately half (53%) of the mean difference in the maximum MCA flow velocity, 90 evaluable patients will have 80% power to detect a statistically significant difference between treatment arms using a 1-sided type 1 error rate of 5%. Statistical significance will be declared if the 2-sided p-value is  $<0.05$ , in this case the trial will have  $>80\%$  power with 90 evaluable patients if the standard deviation is  $<59\%$  of the mean difference.

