**Table 1. TCD Recordings**

| Reading                                           | Units/Response |
|---------------------------------------------------|----------------|
| Left Middle Cerebral Artery Mean Flow Velocity    | cm/s           |
| Right Middle Cerebral Artery Mean Flow Velocity   | cm/s           |
| Left Internal Cerebral Artery Mean Flow Velocity  | cm/s           |
| Right Internal Cerebral Artery Mean Flow Velocity | cm/s           |
| Assessment Performed                              | Pre/Post       |
| Lindergaard Ratio Left                            | none           |
| Lindergaard Ratio Right                           | none           |

The primary endpoint is defined as the maximum of all left middle cerebral artery mean flow velocities (MCA-MFV) and right MCA-MFV values recorded after the first dose of randomised therapy including any taken after Day 7.

Baseline values will be defined as:

- The lowest of the left and right MCA-MFV values recorded at the earliest TCD assessment made within 2 days of first dose
- If a patient does not have a TCD recorded within 2 days of dosing, a predicted baseline value will be imputed based on their age, WFNS score (1 to 5), a past medical history of hypertension (yes/no), surgical procedure (clipping, coiling, none), log-CRP and centre as described below.

Amongst patients with baseline values recorded within 2 days of dosing, their baseline value will be regressed on age, WFNS score, hypertension, surgical procedure, log-CRP and centre. The imputed value for patients with a missing baseline value will equal  $\mu + \sum x_{ij}\beta_j$  where  $x_{ij}$  represent the observed values of the  $j$  covariate levels for the  $i^{\text{th}}$  patient and  $\beta_j$  the corresponding parameter estimates from the regression amongst patients with observed baseline values.

Supplementary analyses will also be performed on the mean of the three largest right or left MCA-MFV recorded at any timepoint after dosing. Additionally, an analysis will be performed to describe the effect over time with timepoints grouped, relative to date of Ictus, as Days 3-4, 5-6, 7-9, 10-14, 15-21, 22-28. Within each timepoint the largest MCA-MFV value will be included in the analysis for each patient. For these two analyses, the same baseline as the primary analysis will be used. Using the timepoint analysis the mean effect of Days 5 to 9 will also be estimated.

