## EVG001SAH Statistical Analysis Plan

```

REPEATED vis / type=un subject=pat;
LSMEANS trt*vis / slice=vis;
RUN;

```

The mean effect over days 5 to 9 will be estimated from the same model using an appropriate ESTIMATE statement weighting each timeperiod equally.

The treatment effect for each analysis will be presented in terms of a ratio (SFX-01:placebo), representing the ratio of the geometric lsmeans (glsmean) for each treatment arm, together with its 95% confidence interval. The glsmean for each arm will be calculated by exponentiating the lsmeans produced from the analysis of the loge-transformed data.

The assumptions of normality will be assessed by normal probability plots of the residuals and plotting standardized residuals versus predicted values.

Many of the baseline values used in the analysis will have been recorded shortly after the patient has been dosed with randomized treatment but before it is anticipated any treatment effect will emerge, will be included. If there is any evidence that SFX-01 has had an effect by Day2 a sensitivity analysis will be performed where the baseline term is removed from the ANOVA model and centre is added to the list of covariates.

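### The primary TCD model and the MMRM leave out centre, a stratification factor after the amendment, without giving a reason; if centre still matters after baseline, the test is conservative and some power is lost

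*SAP*

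**What the plan says.** Randomisation: Section 3 (repeated in Section 6.1) records a change part way through recruitment to "stratify the randomisation by WFNS score (1-3 v 4-5) and centre".

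Primary model: Section 6.4 specifies an ANOVA on log maximum post-dose MCA mean flow velocity with treatment, baseline and "WFNS grade (1-3 v 4-5), hypertension (yes vs no), surgical procedure (clipping vs coiling vs none), log-CRP and age fitted as a continuous covariate". The mean of the three largest velocities and the maximum Lindergaard ratio use the same methods. The MMRM takes the same covariates, and its example code has no centre variable in either the CLASS or the MODEL statement.

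Centre appears in three other places in the TCD work:

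- Section 5.1: a missing baseline is predicted from a covariate list ending in "log-CRP and centre as described below".
- Section 6.4, last paragraph: if SFX-01 seems to have acted by Day 2, a sensitivity analysis drops baseline and "centre is added to the list of covariates".
- Section 6.8: centre is a subgroup variable. If heterogeneity is seen, the interaction model contains the primary terms plus the subgroup main effect.

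Section 6.9 gives greater power through covariates as the reason for modelling.

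**The concern.** One of the two stratification factors is in the model and the other is not, and the SAP does not say why. Elsewhere it treats centre as a useful predictor of TCD velocity.

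Stratifying by a prognostic factor balances it between arms and so makes the treatment estimate less variable. A model without the factor leaves its variance in the residual, so the reported standard error does not reflect that gain. The interval is then wider than it need be and the test rejects too seldom. For patients randomised before the amendment, centre was not balanced by design. For them, omission costs precision and leaves any chance imbalance by centre uncorrected.

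Both effects require centre to explain outcome variance that baseline, WFNS, hypertension, procedure, CRP and age do not. What is at stake is the efficiency of the primary analysis.

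**Working it through.** **1. The plan's own power figure.** Section 3.1 states: "If the standard deviation is approximately half (53%) of the mean difference in the maximum MCA flow velocity", then "90 evaluable patients will have 80% power to detect a statistically significant difference between treatment arms", at a one-sided 5% level. Assume 1:1 allocation (the SAP does not give the ratio), so n = 45 per arm, and

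power = Φ(d·√(n/2) − z), with d = difference/SD and √(45/2) = 4.743.

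- As worded, SD = 0.53 × difference, so d = 1.89 and power is about 100%. The stated 80% is not reproduced.
- Inverted, d = 0.53, one-sided 5%: Φ(2.514 − 1.645) = 80.8%. This reproduces it.
- Inverted, d = 0.59, two-sided 5% (Section 3.1's second statement): Φ(2.799 − 1.960) = 79.9%. This reproduces it.

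The ratio in Section 3.1 is therefore written upside down, which is a separate point. The steps below use d = 0.59, two-sided, because significance will be judged on a two-sided p-value.

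**2. Effect of omitting centre when all patients are stratified by it.** Let r be the share of residual variance, after the other covariates, that centre explains. The SAP does not give r, so 0%, 5%, 10% and 20% are assumptions. The true standard error is √(1−r) times the one that the model without centre reports.

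- Interval width without centre, relative to with it: 1/√(1−r)
- Actual two-sided error without centre: 2·[1 − Φ(1.960/√(1−r))]
- Power with centre: Φ(2.799/√(1−r) − 1.960)
- Power without centre: Φ((2.799 − 1.960)/√(1−r))

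| r | Interval wider by | Actual error | Power without centre | Power with centre | Points lost |
|---|---|---|---|---|---|
| 0% | 0% | 5.0% | 79.9% | 79.9% | 0 |
| 5% | 2.6% | 4.4% | 80.5% | 81.9% | 1.4 |
| 10% | 5.4% | 3.9% | 81.2% | 83.9% | 2.7 |
| 20% | 11.8% | 2.8% | 82.6% | 87.9% | 5.3 |

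The formulas ignore the degrees of freedom that centre uses.

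**3. Simulation check.** Assumptions: 90 patients, 3 or 8 centres of unequal size, blocks of 4, half or all patients stratified, other covariates fitted, 2,000 runs per scenario.

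- r = 20%: power is 76–78% without centre and 83–85% with it. The type I error is 3.5–4.2% without centre and 4.8–6.2% with it. The simulation standard error near 5% is √(0.05 × 0.95/2000), about 0.5 points.
- r = 5%: the power difference is within simulation error.
- r = 0%: no gain. With 8 centres the interval goes from about 0.87 SD without centre to 0.88–0.90 SD with it.

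At r = 20% the simulated error without centre stays above the formula's 2.8%, even with every patient stratified. The error figures in the table are best read as the limit of the conservatism.

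**4. Degrees of freedom.** The primary model uses 9 parameters: intercept, treatment, baseline, WFNS, hypertension, two for procedure, log-CRP and age. With 90 patients, 90 − 9 = 81 residual degrees of freedom remain. Centre takes (number of centres − 1) of them.

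**The case against.** The best defence is that baseline already carries the centre differences. Section 5.1 uses centre to predict the baseline value, and Section 6.4 brings centre in only when baseline is removed. On that reading centre stands in for baseline and the plan is coherent. This stands in part: r may be small, and at zero a centre term only uses degrees of freedom. It is not assured, though. Baseline is the lower side at one early assessment, while the outcome is the highest of all later readings, which continue for as long as they are clinically indicated. If local follow-up practice differs, an early baseline would not capture it. That practice differs is an inference; the SAP gives no data on it.

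It is also fair to say that stratification covered only part of recruitment, and that the per-protocol exclusions and analysis by treatment received loosen the centre balance further. Full stratification is therefore a limiting case. Section 6.8 also examines centre. It re-runs the model within each centre of at least 10 patients and, if heterogeneity is seen, fits centre and baseline together. This is conditional subgroup work and does not replace the main analysis.

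A reader might infer larger harm by pairing the 2.8% error with a power gain from 80% to about 88%, equivalent to 1/(1−0.20) = 1.25 times the patients. These do not belong together. The error figure assumes that all patients are stratified. The gain of about 8 points assumes that none are, since stratification itself already raises power without centre to 82.6%. With full stratification the gain at r = 20% is 5.3 points.

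**Conclusion.** The omission is real, unexplained and at odds with the SAP's stated aim of gaining power from covariates. Its consequence is conditional and modest. If centre explains 5% to 20% of the residual variance and all patients are stratified, the interval is about 3% to 12% too wide and about 1 to 5 power points are lost. The actual error falls to between 4.4% and 2.8%. These rest on assumed shares, 45 patients per arm and a standardised difference of 0.59. None of the three quantities that set the true size (residual centre share, number of centres, proportion stratified) is in the SAP.

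A reader might conclude that the primary result would be biased or the false-positive rate raised. The documents do not support that: the test errs in the conservative direction, and imbalance before the amendment is a matter of chance. Nor do they show that power is certainly lost, because the SAP nowhere says that centre predicts post-dose velocity once baseline is fitted. The change is worth making because it is cheap and follows the design.

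**What to change.** Before unblinding, amend Section 6.4 as follows:

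- Add centre as a factor to the primary ANOVA, the mean-of-three and Lindergaard models, and the MMRM (both CLASS and MODEL statements). Keep baseline and WFNS 1–3 v 4–5.
- Fix a pooling rule for small centres in advance, for example fewer than 10 patients, the threshold Section 6.8 already uses.
- Report the model without centre as a sensitivity analysis.

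If the sponsor prefers the present model, the minimum is a sentence justifying the omission and an unconditional sensitivity analysis with both baseline and centre.

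The cost is one model term, a short text change and (number of centres − 1) of about 81 residual degrees of freedom. If centre has no residual effect, the price is a slightly wider interval. Deciding now avoids a choice between the two models after the results are known.

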## EVG001SAH Statistical Analysis Plan

```

REPEATED vis / type=un subject=pat;
LSMEANS trt*vis / slice=vis;
RUN;

```

The mean effect over days 5 to 9 will be estimated from the same model using an appropriate ESTIMATE statement weighting each timeperiod equally.

The treatment effect for each analysis will be presented in terms of a ratio (SFX-01:placebo), representing the ratio of the geometric lsmeans (glsmean) for each treatment arm, together with its 95% confidence interval. The glsmean for each arm will be calculated by exponentiating the lsmeans produced from the analysis of the loge-transformed data.

The assumptions of normality will be assessed by normal probability plots of the residuals and plotting standardized residuals versus predicted values.

Many of the baseline values used in the analysis will have been recorded shortly after the patient has been dosed with randomized treatment but before it is anticipated any treatment effect will emerge, will be included. If there is any evidence that SFX-01 has had an effect by Day2 a sensitivity analysis will be performed where the baseline term is removed from the ANOVA model and centre is added to the list of covariates.

## 6.5 Analysis of Secondary Efficacy Endpoints

The mRS, GOSE, SAHOT and CLCE will be analysed using a proportional odds logistic regression model to each timepoint separately including the following covariates: treatment, age (fitted as continuous variable), WFNS score (fitted as a class variable), hypertension (yes vs no), surgical procedure (clipping vs coiling vs none) and log-CRP. The treatment effect will be described using an odds ratio together with its likelihood ratio based 95% confidence interval. The statistical significance of the treatment effect will be taken from the chi-square test for the difference in deviance when removing treatment from the model. GOSE scores will be reversed prior to analysis so the odds of a better response is being modelled. PROC LOGISTIC can be used to analyse the data. If the model does not converge, any covariates that are not statistically significant will be removed in order from least significant until the model converges. If the model still does not converge, the outcome level with the fewest observations will be combined with the next most severe outcome and this process repeated until convergence is achieved.

BICRO and SF-36 will be analysed using Van-Elteren's test with 4 strata defined by age (above and below the median) and WFNS score (1-3 v 4-5). The treatment effect will be described using an un-stratified Hodges-Lehmann (HL) estimate of median difference together with its 95% confidence interval. The test can be implemented in SAS as follows:

```

proc npar1way data=data1 HL;
  strata strata/wilcoxon;
  class trt;
  var resp;
run;

```

The proportion of patients with delayed cerebral ischaemia, new cerebral infarct and receiving triple H therapy will be analysed using logistic regression with the same set of covariates used for mRS. The statistical significance of the treatment effect will be taken from the chi-square test for the difference in deviance when removing treatment from the model. The treatment

effect will be described in terms of an odds ratio together with its likelihood ratio based 95% confidence interval.

The length of acute hospital stay will be analysed using a Cox proportional hazards model with the same set of covariates used for mRS. The statistical significance of the treatment effect will be taken from the chi-square test for the difference in deviance when removing treatment from the model. The treatment effect will be described in terms of a hazard ratio together with its profile likelihood 95% confidence interval. In addition, the median will be reported and taken from the 50th percentile of the associated Kaplan-Meier curves.

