## 6 Statistical Methods

### 6.1 General Considerations

All data will be described and analysed according to treatment arm (SFX-01, Placebo) and day and time of assessment (if appropriate), for each patient population (PP, ITT, Safety, sub-study PK).

A (two-sided) significance level of 5% ( $<0.05$ ) will be implemented throughout. The null hypothesis assumed throughout is that there is no difference between the active treatment and the control for any comparison performed (SFX-01 vs Placebo).

Part way through the trial the randomization was amended to stratify by WFNS score (1-3 v 4-5) and centre. For purposes of analyses that are stratified, WFNS score will be taken from the CRFs for patients randomized prior to the amendment and from the random scheme for patients randomized after the amendment.

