## **6.9 Changes from Protocol**

## EVG001SAH Statistical Analysis Plan

1. The use of modelling rather than hypothesis testing where possible to allow more powerful analysis through inclusion of covariates and the generation of treatment estimates with confidence intervals.
2. Refinement of the per-protocol definition to consist of patients who receive at least 10 doses of randomised treatment within the first 7 days post-ictus and to exclude patients with potential dispensing errors.
3. Clarification that mRS and GOSE at 90 days are key secondary endpoints

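### BICRO-39 and SF-36 could be tested with the covariates that the SAP uses for every other clinical endpoint in section 6.5: a cheap gain in power, not the correction of an error

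*SAP*

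**What the plan says.** Section 6.5 tests BICRO-39 and SF-36 by a Van Elteren "test with 4 strata defined by age (above and below the median) and WFNS score (1-3 v 4-5"). The effect is reported as an "un-stratified Hodges-Lehmann (HL) estimate of median difference together with its 95% confidence interval".

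For mRS, GOSE, SAHOT and CLCE the same section fits a proportional odds model with "treatment, age (fitted as continuous variable), WFNS score (fitted as a class variable"), and with "hypertension (yes vs no), surgical procedure (clipping vs coiling vs none) and log-CRP". That covariate set is reused for delayed cerebral ischaemia, new infarct, triple H therapy and length of stay. The primary TCD model in section 6.4 uses the same prognostic factors plus baseline.

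Section 6.9, item 1, lists as a change from the protocol: "The use of modelling rather than hypothesis testing where possible to allow more powerful analysis through inclusion of covariates". The sentence goes on to name a second purpose, treatment estimates with confidence intervals.

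Section 6.3 names mRS and GOSE at 90 days as the key secondary endpoints. It allows a BICRO subscale to be called significant only if the overall BICRO score is significant at the same timepoint.

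**The concern.** BICRO-39 and SF-36 are the only clinical endpoints in section 6.5 that do not use hypertension, surgical procedure and log-CRP, and the only ones where age is cut in two. The SAP gives no reason. A bounded score that includes deaths is a reason to work with ranks, but not a reason to drop covariates, because a rank-based analysis can carry them.

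At stake is the sensitivity of eight main comparisons: two SF-36 scores at three timepoints (6) plus overall BICRO at two (2). A further 16 subscale tests (8 subscales at 2 timepoints) depend on overall BICRO through the condition in section 6.3.

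**Working it through.** **The plan's own power figure.** The SAP states no power for BICRO-39 or SF-36. Its only power statement, in section 3.1, concerns the TCD endpoint: "90 evaluable patients will have 80% power to detect a statistically significant difference". With 45 per arm (assumed equal allocation), power = Φ(δ/SD × √(45/2) − z):
- difference = 0.53 SD, one-sided 5%: Φ(0.53 × 4.743 − 1.645) = 80.8%
- difference = 0.59 SD, two-sided 5%: Φ(0.59 × 4.743 − 1.960) = 79.9%

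The figures reproduce when the difference is read as a fraction of the SD. As worded, with the SD a fraction of the difference, power would be about 100%. That is a separate matter. From here the test is two-sided, following section 6.1: "A (two-sided) significance level of 5"%.

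**Inputs for this point.** About 90 per-protocol patients, from the SAP. The shares of outcome variance explained are not in the SAP and are assumed: WFNS 15%, age a, the three omitted covariates together o.

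**Analytic approximation.** A median split of a normally distributed covariate keeps 2/π = 64% of what it explains. Residual variances are then:
- stratified: 1 − 0.15 − 0.637a
- full adjustment: 1 − 0.15 − a − o

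Set the stratified test at 80% power, so that its standardised effect is 1.960 + 0.842 = 2.802. Power under full adjustment = Φ(2.802 × √(stratified/full) − 1.960).

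| a, o | Residual variance, stratified / full | Power, full adjustment | Power if only the age cut is undone (o = 0) |
|---|---|---|---|
| 5%, 5% | 0.818 / 0.750 | 83.3% | 80.9% |
| 10%, 10% | 0.786 / 0.650 | 86.9% | 81.8% |
| 15%, 15% | 0.755 / 0.550 | 90.7% | 82.9% |

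The age cut alone therefore costs 0.9 to 2.9 points. The rest comes from the omitted covariates.

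**Simulation of the two tests.** n = 90, effect 0.5 SD, 8% of patients tied at the worst value. Power of Van Elteren v rank ANCOVA (linear regression of the overall ranks on treatment and all covariates, treatment t-test):

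| Age, other three | 6000 replicates | 4000 replicates |
|---|---|---|
| none beyond WFNS | 64.9 v 64.2 | 67.1 v 66.9 |
| 5%, 5% | 66.2 v 68.8 | 69.5 v 71.8 |
| 10%, 9% | 67.6 v 74.9 | 69.3 v 75.8 |
| 15%, 12% | 72.0 v 81.0 | 72.8 v 81.0 |

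A third run at the same sample size and effect gave, in the same order, 65.7 v 65.9, 68.1 v 71.5, 70.0 v 76.8 and 72.3 v 81.5. The gains across the three prognostic settings are thus 2.3 to 9.2 points. With an effect of 0.56 SD, 12% at a common worst score and no prognostic value beyond WFNS, Van Elteren is ahead, 76.9 v 75.1. Rejection under the null was between 4.1% and 6.1% for the two tests over all runs.

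**Missing CRP.** Van Elteren needs only age and WFNS. A complete-case rank ANCOVA drops patients without CRP. Van Elteren v rank ANCOVA with 0, 5 and 10% of CRP missing (assumed rates):
- age 5%, others 5%: 68.6 v 72.2; 68.1 v 68.6; 69.2 v 66.8
- none beyond WFNS: 68.0 v 66.8; 67.3 v 64.0; 67.3 v 61.2

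Filling missing log-CRP with its mean restores rank ANCOVA to 71.1, 76.2 and 80.5% in the three prognostic settings of the third run, against 71.5, 76.8 and 81.5% with complete data.

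**Rank of deaths.** Section 5.9 gives a death the worst BICRO score, 5. Section 5.7 sets all SF-36 items to 0 for a death and then derives the component scores as 50 + 10 × Σ coefficient × (subscale − mean)/SD. With Table 6, all subscales at 100 give 57.87 and 62.14, as the SAP states. All subscales at 0 give sums of −2.986 and −3.266, so a death scores 50 − 29.86 = 20.1 (Physical) and 50 − 32.66 = 17.3 (Mental). Some coefficients are negative, so the minimum has 100 on those subscales and 0 on the rest: 1.7 and −1.3. A survivor with PF 5, RP 0, RE 100, VT 40, EW 80, SF 50, BP 45 and GH 30 scores Physical 15.6, below a death.

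**The case against.** The strongest reply is that this is a preference between valid methods. Van Elteren with prespecified strata is already an adjusted test. It uses WFNS, a randomisation stratum for part of the trial, and age, and its type I error is sound. That stands.

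A reader might infer that section 6.5 contradicts section 6.9. The documents do not support this. Item 1 is qualified by where possible, so exceptions are foreseen. Its second purpose is estimates with intervals, which rank ANCOVA alone does not give on the score scale. What remains is an unexplained departure from a stated aim. Keeping the Hodges-Lehmann estimate meets the point about scale, although that estimate stays unadjusted, as already planned.

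A reader might also suppose that ranking the score keeps death as the worst outcome. That holds for BICRO-39 but not for SF-36, which is six of the eight main comparisons. Placing deaths last on SF-36 would change the rule in section 5.7.

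The objection about missing CRP is right for a complete-case fit: at 10% missing the gain shrinks or reverses. It does not hold once missing values are filled. Last, every magnitude rests on assumed shares, and the range includes zero. That stands too, although by fitting these covariates elsewhere the SAP already treats them as prognostic.

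**Conclusion.** The point holds as a cheap improvement. At n = 90 the planned tests give up about 3-9 points of power if age explains 5-15% of the outcome and hypertension, surgery and CRP together 5-12%. The loss is nil or slightly reversed if they explain nothing beyond WFNS. These shares, the effect size and the proportion of deaths are assumptions, as the SAP gives none of them.

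Two stronger readings should be avoided. The median split of age is not the main problem: it accounts for about 1-3 points. And no conclusion is biased or invalid. The primary endpoint and the key secondary endpoints already carry the full covariates, and no power is claimed for BICRO-39 or SF-36. The impact is minor.

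**What to change.** Before unblinding, amend section 6.5 as follows:
- Test BICRO-39 and SF-36 by rank ANCOVA of the score as the SAP derives it, with treatment, WFNS (1-3 v 4-5), continuous age, hypertension, surgical procedure and log-CRP.
- Fill missing covariate values by a simple rule blind to arm, for example the overall mean of log-CRP, so that no patient is dropped.
- Keep the Hodges-Lehmann estimate and interval for the size of the effect, and Van Elteren as a sensitivity analysis.
- State whether SF-36 is ranked on the derived component score or with deaths placed last. The second option changes section 5.7 and should be declared as such.

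The proportional odds likelihood-ratio test used for mRS should not simply be carried over. On a near-continuous score it rejected about 7-8% under the null in the weakest-covariate setting simulated.

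The cost is SAP wording and a few lines of code, with no new data. The downside is up to about 1-2 points of power if the covariates are not prognostic, and more if patients with missing CRP are dropped. If the sponsor prefers Van Elteren as the main test, a sentence giving the reason for the exception would close the point.
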